Specifically, in Chile, the impact of such interventions on variables such as mental health, physical activity, physical fitness, motor competence, and academic performance in school-age populations remains unknown. In particular, the potential effect of this type of classroom intervention on mental health and climate problems in Chilean schools is unknown. It is of clinical and public health relevance to understand whether active teaching methodologies, such as video-guided school active breaks in the classroom, can improve the wellbeing of Chilean schoolchildren and thus address the problems of mental health and climate in Chilean schools. Therefore, due to the lack of studies examining the effects of video-guided active breaks on mental health and school climate, this study aims to describe the methods and rationale of an active breaks intervention (“Active Classes + School Climate and Mental Health”) to improve mental health and school climate (primary outcome), physical activity, physical fitness, motor competence, and academic performance (secondary outcomes) in 6 to 10-year-old schoolchildren in the Biobío region of Chile.

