### Primary outcome variables

#### Mental health

The mental health of students will be assessed through self-esteem and socioemotional wellbeing. Self-esteem will be evaluated using a School Self-Esteem Test. This scale, developed and validated in Chile by (Marchant et al., 2001), awards one point for each positive response and zero for each negative response. The raw score sum is transformed into a T score according to age norms, categorizing students as follows: normal self-esteem, ≥40 points; low self-esteem, 30–39 points; and very low self-esteem, ≤29 points. The internal consistency level achieved in this questionnaire with the current sample achieved a Cronbach’s alpha of 0.81. This variable will be assessed in students of 3rd and 4th grade during the study.

Two instruments will be used to assess socioemotional wellbeing. A) Self-report of socioemotional wellbeing. This scale, developed and validated in Chile by Edwards et al. (2022), will be evaluated in students of 1^st^ and 2^nd^ grade during the study. The questionnaire has adequate psychometric properties in terms of test-retest reliability for different socioeconomic levels (correlations range from 0.761 to 0.949) and internal consistency for the entire test (Cronbach’s Alpha of 0.82). B) The Integral Learning Diagnosis. This instrument, implemented by the Education Quality Agency, is applied three times per year. There is an initial evaluation at the beginning of the year, an intermediate evaluation, and a final evaluation. For this study, the evaluative socioemotional activity test (1st, 2nd, and 3rd-grade students) and the Socioemotional Questionnaire (4th-grade students) were used at three points: the beginning, middle, and end of the school year. The evaluative socioemotional activity is a space for expression and dialogue that assesses the socioemotional skills of girls and boys according to their level, which was evaluated in previous application periods: self-awareness, awareness of others, inclusion, collaboration and communication, empathy, pro-sociality, self-regulation, and democratic commitment. The socioemotional questionnaire collects information about students’ perceptions in two areas: socioemotional learning - both in themselves and regarding the school’s management - and key aspects of comprehensive training (Agencia Nacional de Educación, 2022).

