#### School climate

The Social Climate Scale developed by Aron et al. (2012) will be used. The social climate scale includes 82 items with a four-level Likert-type response format (ranging from all to none). For this study, only three subscales will be considered: teachers (30 items, e.g., “they are reliable,” “they notice when someone has problems”; Cronbach’s alpha reliability index of .84), peers (15 items, e.g., “My classmates laugh at me,” “I know how to share”; Cronbach’s alpha of .81), and the school context (ten items, e.g., “My school is clean and well-organized,” “I have enough working materials in my classroom”; Cronbach’s alpha of .68) (Aron et al., 2012). This variable will be assessed in students of 3^rd^ and 4^th^ grade during the study. This instrument is completed by the students.

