### Statistical analysis

Missing data will be handled using intention-to-treat analysis (multiple imputation method) (Sterne et al., 2009). Descriptions will be performed as measures of central tendency and dispersion (continuous variables) and as percentages (categorical variables). Using the Shapiro-Wilk test, the normality of the data will be checked, and a two-step approach will be applied to transform non-normal variables (Templeton, 2011). Homoscedasticity will be analyzed using the Levene test. A two-way repeated measures analysis of variance (ANOVA) will be used to determine the effects of the interventions. The model effects are group (TG; CG), times (Pretest; Posttest), and their interaction over time (Time x Group). The Bonferroni *post hoc* test will be applied to identify statistically significant comparisons. Effect size (ES) will be determined using Cohen’s d (<0.2 insignificant; ≥0.2 and ≤0.49 small; ≥0.5 and ≤0.79 moderate; ≥0.8 large) (Cohen, 1988). Data will be analyzed using SPSS software (version 26 for Windows, IBM, New York, USA).

Missing data will be handled by a non-parametric missing value method using a random forest via the R package “missForest” of R statistical software (version 4.4.1). This function successfully imputes large and complex data sets of mixed type (quantitative and/or categorical variables), including complex interactions and non-linear relationships, using a random forest trained on observed values that predict missing values.

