Mixed model analyses will be carried out to establish differences in school climate and mental health between the experimental group (video-guided active breaks incorporating curricular content within the school classroom setting) and the control group. The fixed effects of the model are group (Experimental versus control), times (Pretest; Posttest), and their interaction over time (Time x Group). The schools in the models will have a random effect to capture the hierarchical structure of the data and handle the possible dependence of observations within each school. To compare the probability of a model with the effect included versus a model with the effect excluded, the likelihood ratio test (LRT) will be used for the random effect. Additionally, the intraclass correlation coefficient (ICC) will be estimated to quantify the proportion of the total variance attributed to the variance between clusters (schools). Post-hoc tests will be performed using Holm’s correction for multiple comparisons. For all analyses, a significance level of *p* < 0.05 was established. Models will adjust for multiple covariates, such as demographic characteristics (e.g., age, gender) and secondary study variables, that could influence school climate and mental health outcomes. All analyses will be performed using Jamovi statistical software version 2.0.0.0 (The Jamovi Project).

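### Seven named primary scores, p < 0.05 for every analysis, and corrections confined to post-hoc tests leave error across the primary Time x Group tests uncontrolled

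*Protocol article*

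**What the plan says.** The Introduction of the protocol article states the aim as "to improve mental health and school climate (primary outcome", so two constructs share the primary label. The Discussion repeats this.

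The two primary-outcome subsections then name the measures:

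- **Self-esteem** (grades 3 and 4 in the text): "Self-esteem will be evaluated using a School Self-Esteem Test".
- **Socioemotional wellbeing**: "Two instruments will be used to assess socioemotional wellbeing". The first is a self-report for grades 1 and 2. The second is the DIA, which takes two forms by grade: "the evaluative socioemotional activity test (1st, 2nd, and 3rd-grade students) and the Socioemotional Questionnaire (4th-grade students) were used at three points".
- **School climate** (grades 3 and 4): "For this study, only three subscales will be considered", namely teachers, peers and school context. Each has its own reliability coefficient. No total score is described.

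On error control, the Statistical analysis section says "For all analyses, a significance level of *p* < 0.05 was established". For the repeated measures ANOVA it adds "The Bonferroni *post hoc* test will be applied to identify statistically significant comparisons", and for the mixed models "Post-hoc tests will be performed using Holm’s correction for multiple comparisons". It states no other multiplicity rule.

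**The concern.** With two groups and two times, the treatment effect on any one score is a single Time x Group term. Post-hoc tests in such a model compare the four group-by-time cells within one outcome, and no pairwise cell comparison is the interaction itself. A correction attached to post-hoc tests therefore neither adjusts the treatment-effect test nor reaches from one outcome to another. A reader who sees Holm and Bonferroni named could believe that multiplicity is handled when, for the primary claim, it is not.

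The article hopes that its results will inform ministerial and school-level programmes. One nominally significant subscale out of several could be presented as an effect on school climate or mental health, although the error rate behind that claim is not the stated 5%.

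**Working it through.** **The plan's own figure.** The article states only the per-test level of 0.05. It gives no familywise error rate, so there is none to reproduce. Sidedness is not stated; two-sided tests are assumed below.

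**Counting the named scores.** Mental health: self-esteem test, wellbeing self-report, DIA activity, DIA questionnaire = 4. School climate: three subscales = 3. Total 4 + 3 = 7. This counts named scores. The article does not say how many models will be fitted.

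**Familywise error if independent.** For k tests at 0.05, the chance of at least one false positive when nothing works is 1 − 0.95^k.

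| Reading of the primary set | k | 1 − 0.95^k |
|---|---|---|
| All named scores | 7 | 30.2% |
| DIA forms treated as one | 6 | 26.5% |
| One climate total | 5 | 22.6% |
| Both mergers | 4 | 18.5% |
| One test per construct | 2 | 9.8% |

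Within constructs, the four mental health tests give 18.5% and the three climate tests 14.3%.

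**Why independence is an upper bound here.** Seven scores form 7 × 6 / 2 = 21 pairs. By the grades given in the text, the pairs on disjoint grades are the wellbeing self-report with self-esteem (1), with the three climate subscales (3) and with the DIA questionnaire (1), plus the DIA activity with the DIA questionnaire (1). That makes 6, so 15 of the 21 pairs share pupils. Every pair also shares the same six randomised schools. Positive correlation lowers the familywise rate.

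**With correlation.** The article gives no correlation, so a range is assumed. Simulation of seven equicorrelated normal test statistics, 400,000 draws:

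| Assumed correlation | Any false positive | Favourable direction only | Any, with Holm across seven |
|---|---|---|---|
| 0 | 30.2% | 16.2% | 4.9% |
| 0.3 | 27.1% | 13.7% | 4.6% |
| 0.5 | 22.9% | 11.5% | 4.1% |
| 0.7 | 17.9% | 9.0% | 3.2% |

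The favourable figure at correlation 0 agrees with 1 − 0.975^7 = 16.2%. For two independent tests it is 1 − 0.975^2 = 4.9%.

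**Thresholds.** Holm's first step is 0.05/k: 0.05/7 = 0.0071 for seven tests and 0.05/2 = 0.025 for two.

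**The case against.** The strongest reply is that the article never says that seven tests will be run. The mixed models are described only as comparing the two constructs, and scoring and the testing family are often left to an analysis plan. This stands in part. Seven is the number of named scores and not a planned minimum of tests: merging the DIA forms or totalling the climate subscales would give four to six. It does not remove the point, because the article goes beyond silence. It fixes 0.05 for all analyses and fixes the scope of both corrections, so an analysis plan that followed this text would carry the gap forward.

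Three stronger readings are tempting and are not supported:

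- A reader might infer that a false claim is likely. At 18–30% for any false positive, and 9–16% for a favourable one, it is not.
- A reader might count 15 tests, by scoring the eight DIA skills and the two questionnaire areas separately. The article lists these but does not say that they will be analysed separately.
- A reader might infer that the post-hoc tests are mainly before-after comparisons within arm. Four cells give six pairwise contrasts: two within arm, two between arms at the same time and two crossed. The article does not say which will be run.

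A further objection is that strict thresholds are costly with six schools. If inference used 4 degrees of freedom (an assumption; the article does not state it), the two-sided critical t would rise from 2.78 at 0.05 to 5.07 at 0.0071, against 3.50 at 0.025. That does not defeat the correction, but it is a good reason to offer the two-measure option.

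**Conclusion.** The concern holds in this form: several primary scores, no lead measure, and no control of error across the primary Time x Group tests. If all seven scores are tested at 0.05, the familywise error is about 18–30%, with 30.2% the bound under independence and 17.9% at an assumed correlation of 0.7. If only one test per construct is run, it is at most about 10%. Under the counts from two to seven and the correlations shown, the rate exceeds the stated 5%.

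The figures assume two-sided tests, no true effect on any score, and that each test holds its own 5% level. They count one model per score. The ANOVA is not restricted to particular outcomes, so it may test the same scores a second time, and that is not counted here.

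**What to change.** Before analysis, designate one primary model and choose one of two rules:

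1. Apply the Holm procedure, already named in the article, across the family of primary Time x Group tests from that model. For seven scores the smallest p-value must be below 0.0071.
2. Name one primary measure for mental health and one for school climate, and apply Holm to those two, with a first threshold of 0.025. Report the remaining scores as secondary.

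Under either rule, base the primary claim on the adjusted p-value of the interaction and not on post-hoc contrasts between cells.

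The change is to wording only and needs no new data. Its cost is lower power for each individual score, and this is smaller under the second rule. The second rule also requires the investigators to commit to a lead measure. Because the named instruments cover different grades, that choice also decides which pupils inform each primary claim.

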Physical activity and exercise are recognized as protective factors in the prevention and treatment of various health conditions and are associated with better mental health (Biddle and Asare, 2011; Eime et al., 2013; Hillman and Biggan, 2017; World Health Organization, 2020). High levels of physical activity and fitness in children have been linked to better mental health (Andermo et al., 2020; Poitras et al., 2016; Rodriguez-Ayllon et al., 2019). Additionally, there is recent evidence indicating that a high level of physical activity in childhood develops motor skills related to the level of physical activity in adulthood (Engel et al., 2018). The Global Action Plan on Physical Activity 2018–2030 suggests an inclusive approach in the school environment that promotes the participation and integration of physical activity in various educational contexts (World Health Organization, 2018). Therefore, active commutes, recesses, physical education classes, and especially the classroom, make the school an ideal environment for promoting physical activity and mental health (Langford et al., 2015; Ministerio de Salud, 2017; O’Connor et al., 2018).

Specifically, physical activity interventions in the classroom have a growing body of evidence supporting their positive effects (McDonald et al., 2018), including increased physical activity levels (Masini et al., 2020), academic performance (Bedard et al., 2019; Watson et al., 2017a), cognitive functions (Daly-Smith et al., 2018; Donnelly et al., 2016), attention, and classroom behaviour (Carlson et al., 2018). More recently, two reviews have reported the positive effects of such interventions on indicators associated with the wellbeing and mental health of the school-age population (Papadopoulos et al., 2022; Robles-Campos et al., 2023).

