## Variables and instruments

Characterization variables of schoolchildren reported by the parents were measured through a auto-fill questionnaire only once before the intervention (sociodemographic variables such as birthdate, sex, nationality, place of residence, school, course, class schedule, participation in school integration program and sports activities, type of travel to and from school, usual clothes to wear at school, absence, previous pathologies, vision and hearing were measured with a self-developed instrument. Additionally, consumption, habits and practices of feeding was measured with a validated instrument in Chilean schoolchildren (Vio del Rio, 2015), which will be included as covariates to fit the proposed models in the mixed model analysis. Subsequently, the following variables will be measured in all participants before and after the intervention.

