## Discussion

Currently, education and health are global concerns. There is a well-established and persistent association between the multiple components of education and health. Furthermore, policies that affect educational achievement could have a significant impact on population health (Cutler and Lleras-Muney, 2008). In recent years, there has been growing interest in establishing the benefits of physical exercise on the health of school populations (Dodd et al., 2022). Several school policies and practices have been reported to be effective in improving children’s physical activity; however, schools often do not implement such evidence-based interventions (Wolfenden et al., 2017). Moreover, scientific evidence is lacking regarding the potential benefits to mental health and the classroom climate in developing countries.

This article presents the justification and methodology of the “Active Classes + School Climate and Mental Health” Project, a 12-week program of guided active breaks with curricular content in the school classroom, to test its impact on mental health and school climate (primary outcome), physical condition, and academic performance (secondary outcomes) in students aged 6 to 10 in the Biobío province, Chile.

The study’s findings will be useful in clarifying and objectifying the effects of incorporating active breaks into primary schools. Our hypothesis is that the study results could provide evidence. First, from an educational standpoint, active breaks could be an effective strategy to improve mental health, classroom climate, and academic performance. Secondly, from a health promotion perspective, this school intervention could help reduce sedentary behavior, increase physical activity levels, and improve health-related physical fitness in children.

Guidelines on physical activity and exercise in school settings suggest the importance of supporting the trend of children and adolescents to be more physically active. Therefore, the results of this study could provide new solid evidence for recommendations and facilitate knowledge transfer to practice. Additionally, they can support active breaks as a strategy for an innovative school model focused on student wellbeing in developing countries.

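### The mixed models for the primary outcomes adjust for secondary study variables without limiting them to baseline; if post-test values enter, Time x Group is no longer the total programme effect

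*Protocol article*

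**What the plan says.** The Statistical analysis section assigns the primary outcomes to mixed models: "Mixed model analyses will be carried out to establish differences in school climate and mental health between the experimental group" and the control group. The model terms are given as follows: "The fixed effects of the model are group (Experimental versus control), times (Pretest; Posttest), and their interaction over time (Time x Group"), with a random effect for school. The same paragraph then states: "Models will adjust for multiple covariates, such as demographic characteristics (e.g., age, gender) and secondary study variables". The reason given is that such variables might affect the primary outcomes. Nothing says at which occasion they are taken.

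The Introduction identifies the secondary variables: "physical activity, physical fitness, motor competence, and academic performance (secondary outcomes"). Their timing is in Variables and instruments. That section first describes a parent questionnaire completed once before the intervention, part of which it names as mixed-model covariates. It then continues: "Subsequently, the following variables will be measured in all participants before and after the intervention".

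On what the programme should change, the Discussion says "this school intervention could help reduce sedentary behavior, increase physical activity levels, and improve health-related physical fitness in children". On the link to the primary outcome, the Introduction says "High levels of physical activity and fitness in children have been linked to better mental health".

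**The concern.** The trial asks what the programme does to mental health and school climate, by whatever route. A covariate that the programme itself moves, and that in turn moves the outcome, lies on that route. Holding it fixed removes the part of the effect that passes through it. What remains is a direct effect net of activity and fitness, which is a different quantity.

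That direct effect is also not protected by randomisation. Follow-up fitness or activity may share unmeasured causes with follow-up mental health, such as illness, family circumstances or events at school. Conditioning on the follow-up value then brings confounding into the comparison between arms.

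At stake is the meaning of the main estimate. A programme that worked by raising activity and fitness could look weaker than it is, or even ineffective.

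**Working it through.** **Which values enter.** The article states no power calculation, effect size or SD that bears on this, so there is no figure to reproduce. The first step is to set the statements side by side.

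1. The once-only, pre-intervention variables are named as covariates in their own place, so the phrase about secondary study variables is not another name for them.
2. The secondary variables are measured at pretest and post-test, and the model has a record for each occasion. Entering the value from each occasion is therefore the natural reading.
3. A baseline-only covariate, entered as a main effect, has the same value in a child's two records. It cancels from the within-child change and cannot alter the Time x Group coefficient in complete data. The adjustment affects that coefficient only if post-test values enter.

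**What adjustment would do.** Let *T* be the total effect on the outcome, *a* the programme's effect on the secondary variable, and *b* the slope of outcome on secondary variable. With the variable entered at both occasions and no shared unmeasured cause:

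adjusted Time x Group = *T* − *a* × *b*; share removed = *a* × *b* / *T*.

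All inputs are assumptions: *T* = 0.30 SD, *a* = 0.2 to 0.5 SD, *b* = 0.1 to 0.5.

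| *a* | *b* | *a* × *b* | Adjusted effect (SD) | Share removed |
|---|---|---|---|---|
| 0.2 | 0.1 | 0.02 | 0.30 − 0.02 = 0.28 | 0.02/0.30 = 7% |
| 0.2 | 0.5 | 0.10 | 0.30 − 0.10 = 0.20 | 0.10/0.30 = 33% |
| 0.3 | 0.3 | 0.09 | 0.30 − 0.09 = 0.21 | 0.09/0.30 = 30% |
| 0.5 | 0.3 | 0.15 | 0.30 − 0.15 = 0.15 | 0.15/0.30 = 50% |
| 0.5 | 0.5 | 0.25 | 0.30 − 0.25 = 0.05 | 0.25/0.30 = 83% |

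**Check by simulation.** The simulation used 823 children (the article's sample size), pre and post records, and 200 replicates per scenario. School clustering was left out because it does not bear on this point.

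- Unadjusted Time x Group averaged 0.291 to 0.307 over all scenarios.
- Adjusting for the baseline secondary variable gave the same value as no adjustment, to three decimals, in every scenario.
- Adjusting for the variable at both occasions gave 0.274 at (*a*, *b*) = (0.2, 0.1), 0.207 at (0.3, 0.3) and 0.043 at (0.5, 0.5), in line with the formula.
- With an added cause shared by secondary variable and outcome at each occasion (30% of the occasion-specific variance, same direction on both), those three values fell to 0.255, 0.173 and −0.007.

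A shared cause acting in opposite directions on the two variables would understate *b* and push the adjusted estimate up. The direction is therefore not guaranteed.

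**The case against.** The best defence is that the text never says post-test values are used. Adjusting for variables that might affect the outcome also fits ordinary prognostic adjustment at baseline, and a condensed article may leave the occasion to a fuller plan. This stands in part: the harm is conditional. The sentence still needs changing, because it is a stated analysis choice whose natural reading is the harmful one.

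Second, the same section plans a repeated-measures ANOVA with no covariates listed, so an estimate free of this adjustment would exist. That mitigates the problem but does not cure it. The ANOVA has no school term although whole schools are randomised, and the mixed model is the one named for the primary outcomes.

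Third, a reader might infer that a known part of the effect will be adjusted away. The documents do not support that. The effect size and slopes above are assumptions. The activity measure is also a weak stand-in for the pathway: it is parent-reported, centres on walking, organised sport and active play, and has a Cronbach's alpha of .64 for activity and .23 to .34 for sedentary behaviour. Adjusting for so noisy a measure would remove less than the full share carried by activity.

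Fourth, a reader might treat all the secondary variables as mediators. The link is explicit only for activity and fitness. Academic performance is hypothesised to improve, but as a parallel outcome. For motor competence the Discussion states no separate hypothesis.

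Finally, a reader might expect pupils without secondary measures to be dropped. The section plans imputation, so that does not follow.

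**Conclusion.** The point holds in conditional form. The article commits the primary mixed models to adjusting for secondary variables, does not restrict them to baseline, and by its own account treats activity and fitness as both changed by the programme and related to mental health. If follow-up values enter, Time x Group no longer estimates the total programme effect. Shrinkage toward zero is expected if these variables mediate benefit, but confounding between mediator and outcome could move the estimate either way.

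The size cannot be derived from the documents. The range of 7% to 83% of a 0.30 SD effect shows only how much depends on the unstated choice. It rests on the assumed *a*, *b* and *T*, and on a covariate that fully captures the pathway. With baseline values only, nothing is removed.

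**What to change.** Replace the covariate sentence with a closed list of variables measured before the intervention. For example: *The primary mixed models will adjust for age or grade, sex and province, and no variable measured after the start of the intervention will be included.* Baseline values of secondary variables may be added to the list if wanted. Any analysis that adjusts for follow-up activity, fitness or other secondary variables should be reported separately and labelled as a mediation analysis, with its no-confounding assumptions stated.

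The pretest outcome should stay as a response in the Time x Group model. It should become a covariate only if the model is changed to a post-test ANCOVA, since it cannot sensibly serve as both.

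The restriction costs a sentence or two, with no new data and no change to assessments. Moving to ANCOVA would be a larger rewrite of the model paragraph and is not needed to solve this problem.
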